## Abstract

Cervicogenic headache (CEH) is a secondary headache which affects 1.0–4.6 % of the population. Although the costs are unknown, the health consequences are substantial for the individual; especially considering that they often suffers chronicity. Pharmacological management has no or only minor effect on CEH. Thus, we aim to assess the efficacy of chiropractic spinal manipulative therapy (CSMT) for CEH in a single-blinded placebo-controlled randomized clinical trial (RCT). According to the power calculations, we aim to recruit 120 participants to the RCT. Participants will be randomized into one of three groups; CSMT, placebo (sham manipulation) and control (usual non-manual management). The RCT consists of three stages: 1 month run-in, 3 months intervention and follow-up analyses at the end of intervention and 3, 6 and 12 months. Primary end-point is headache frequency, while headache duration, headache intensity, headache index (frequency × duration × intensity) and medicine consumption are secondary end-points. Primary analysis will assess a change in headache frequency from baseline to the end of intervention and to follow-up, where the groups CSMT and placebo and CSMT and control will be compared. Due to two group-comparisons, the results with p values below 0.025 will be considered statistically significant. For all secondary end-points and analyses, the significance level of 0.05 will be used. The results will be presented with the corresponding p values and 95 % confidence intervals. To our knowledge, this is the first prospective manual therapy three-armed single-blinded placebo-controlled RCT to be conducted for CEH. Current RCTs suggest efficacy in headache frequency, duration and intensity. However a firm conclusion requires clinical single-blinded placebo-controlled RCTs with few methodological shortcomings. The present study design adheres to the recommendations for pharmacological RCTs as far as possible and follows the recommended clinical trial guidelines by the International Headache Society.

*Trial registration* ClinicalTrials.gov identifier: NCT01687881, 2 December 2012

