### Primary and secondary end-points

The primary and secondary end-points are listed in Table 2. The end-points adhere to the recommended IHS clinical trial guidelines (Tfelt-Hansen et al. 2000; Silberstein et al. 2008). We define number of headache days to be primary end-point and expect at least 25 % reduction in average number of days from baseline to the end of intervention, with the same level of reduction maintaining at follow-up. Based on previous reviews on CEH, a 25 % reduction is considered to be a conservative estimate (Chaibi and Russell 2012). A 25 % reduction from baseline to the end of intervention and follow-up is also expected in secondary end-points for headache duration, headache intensity, and headache index, where the index is calculated as mean days with headache (30 days) × mean headache duration (hours per day) × mean intensity (0–10 NRS). A 50 % reduction in medication consumption from baseline to the end of intervention and to follow-up is expected.

**Table 2 Tab2:** Primary and secondary end-points

Primary end-points
1. Number of headache days in active treatment vs. placebo group
2. Number of headache days in active treatment vs. control group
Secondary end-points
3. Headache duration in hours in active treatment vs. placebo group
4. Headache duration in hours in active treatment vs. control group
5. Self-reported VAS in active treatment vs. placebo group
6. Self-reported VAS in active treatment vs. control group
7. Headache index (frequency × duration × intensity) in active treatment vs. placebo group
8. Headache index in active treatment vs. control group
9. Headache medication dosage in active treatment vs. placebo group
10. Headache medication dosage in active treatment vs. control group

The data analysis is based on the run-in period vs. end of intervention. Point 11–40 will be duplicate of point 1–10 above at respectively 3, 6 and 12 months follow-up

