**Fig. 2 Fig2:**
[figure not shown]
Expected participants flow diagram

Change in primary and secondary end-points from baseline to the end of intervention and to follow-up will be compared between active and placebo and active and control group. Null-hypothesis states that there is no significant difference between the groups in average change, while the alternative hypothesis states that a difference of at least 25 % exists.

Due to follow-up period, repeated recordings of primary and secondary end-points will be available, and analyses of trend in primary and secondary end-points will be of main interest. Intra-individual correlations (cluster effect) are likely to be present in data with repeated measurements. Cluster effect will thus be assessed by an intra-class correlation coefficient (ICC) quantifying the proportion of total variation attributable to the intra-individual variations. The trend in end-points will be assessed by a linear regression model for longitudinal data (linear mixed model) to correctly account for possible cluster effect. Linear mixed model handles unbalanced data, enabling all available information from randomized patients to be included, also from drop-outs. Regression models with fixed effects for time component and group allocation as well as the interaction between the two will be estimated. The interaction will quantify possible differences between groups regarding time trend in the end-points and serve as an omnibus test. Random effects for patients will be included to adjust the estimates for intra-individual correlations. Random slopes will be considered. The linear mixed models will be estimated by SAS PROC MIXED procedure. The two pairwise comparisons will be performed by deriving individual time point contrasts within each group with the corresponding p values and 95 % confidence intervals (CI).

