Both per-protocol and intention-to-treat analyses will be conducted if relevant. All analyses will be performed by a statistician, blinded for group allocation and participants. All adverse effects will also be registered and presented. Participants who experience any sort of adverse effects during the trial period will be entitled to call the prime investigator on the project cell phone. The data will be analyzed with SPSS v22 and SAS v9.3. Because of two group-comparisons in a primary end-point, p values below 0.025 will be considered statistically significant. For all secondary end-points and analyses, a significance level of 0.05 will be used. Missing values might appear in incomplete interview questionnaires, incomplete headache diaries, missed intervention sessions and/or due to drop-outs. The pattern of missingness will be assessed and missing values handled adequately.

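### The primary time point is stated inconsistently, and the 0.025 threshold covers the two group comparisons but not the four time points that the abstract puts into the primary analysis

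*Protocol article*

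**What the plan says.** Four places in the protocol article bear on which time point is primary.

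- **Abstract.** "Primary analysis will assess a change in headache frequency from baseline to the end of intervention and to follow-up", for CSMT versus placebo and CSMT versus control. The time points are given as "follow-up analyses at the end of intervention and 3, 6 and 12 months".
- **Methods and design, opening paragraph.** The primary hypothesis is a reduction of at least 25 % in headache days from baseline to the end of intervention. The same reduction is then expected to persist at 3, 6 and 12 months.
- **Primary and secondary end-points, Table 2.** Two primary end-points are listed, one per comparison. The note reads "The data analysis is based on the run-in period vs. end of intervention" and continues "Point 11–40 will be duplicate of point 1–10 above at respectively 3, 6 and 12 months follow-up". It does not say whether the repeated points 1 and 2 remain primary.
- **Data processing.** Change to the end of intervention and to follow-up is compared for all end-points, and "analyses of trend in primary and secondary end-points will be of main interest". A mixed model supplies a group-by-time interaction, called an omnibus test, and contrasts at individual time points.

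On the threshold, Data processing says "Because of two group-comparisons in a primary end-point, p values below 0.025 will be considered statistically significant" and "For all secondary end-points and analyses, a significance level of 0.05 will be used". The Power calculation gives the same reason for 0.025: the primary analysis contains two group comparisons.

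**The concern.** The threshold and the scope of the primary analysis do not match. Dividing 0.05 by two pays for two comparisons at one time point. The abstract's sentence gives each comparison four time points, and no adjustment, order or gate across time is stated anywhere.

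At stake is what counts as a positive trial. A reader holding the abstract could accept a difference significant only at 6 months as a primary result. A reader holding the primary hypothesis and the Table 2 note would not. Background criticises earlier trials for not pre-specifying their end-points, so the time point should not be left to interpretation here.

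**Working it through.** **Inputs from the article.** Two comparisons; four time points; 0.025 per comparison; equal allocation; difference 2.5 days, SD 2.5, 80 % power, 20 per group (Power calculation).

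**Inputs assumed.** Two-sided tests; correlation 0.5 between the two comparisons, because they share the active arm in equal-sized groups; between-time correlation varied from 0 to 0.9, because Data processing says only that such correlation is likely.

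**1. The plan's own figures.** The threshold is 0.05 / 2 = 0.025. The sample size per group is 2 × (2.241 + 0.842)² × (2.5 / 2.5)² = 19.01, rounded up to 20. This matches the article and confirms that the calculation is two-sided and counts two tests. (The exact t calculation gives 79.3 % power at 20 and needs 21, a trivial difference.)

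**2. Number of contrasts under the abstract.** 2 comparisons × 4 time points = 8.

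**3. Simple bounds.**
- Eight tests, Bonferroni bound: 8 × 0.025 = 20.0 %.
- Eight independent tests: 1 − 0.975⁸ = 18.3 %.
- Two independent tests: 1 − 0.975² = 4.9 %.

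**4. With correlation.** Simulation of eight two-sided z tests under the global null, 1,000,000 draws per setting:

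| Between-time correlation | Any of 8 below 0.025 | Multiple of 5 % |
|---|---|---|
| 0 | 17.3 % | 3.5 |
| 0.5 | 14.8 % | 3.0 |
| 0.7 | 12.5 % | 2.5 |
| 0.8 | 11.0 % | 2.2 |
| 0.9 | 9.0 % | 1.8 |

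The two end-of-intervention tests alone give 4.7 % at every setting. A value of 0.5 is what changes from one shared baseline have under a random-intercept model with residual variance σ²: covariance σ² over variance 2σ². A correlation that decays with time (0.7 to 0.9 per 3 months) gives 14.4 % to 10.6 %.

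**5. The omnibus test as a gate.** With time as a category, three groups and five occasions give (3 − 1) × (5 − 1) = 8 degrees of freedom. Requiring this test to be significant at 0.05 first would bring the error under the global null to about 1.5 to 4.2 %, over between-time correlations from 0.99 to 0.

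**6. The alternative of paying for all eight.** At 0.05 / 8 = 0.00625, 80 % power needs 26 per group (normal) or 28 (t). With 20 per group, power falls to 67 % (normal) or 61 % (t). With all 40 per group analysed it is about 95 % (t). The 40 per group covers 28 with up to 30 % drop-out (40 × 0.7 = 28).

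**The case against.** The strongest reply is that the end of intervention is already primary. The hypothesis is worded that way, with follow-up only expected to maintain the effect; the Table 2 note says so; and the Power calculation counts the primary analysis as two comparisons. On that reading the error is 4.7 % and there is no inflation. This stands as a plausible account of the intent. It does not remove the conflict, because the abstract's sentence then says something else and has to be corrected.

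A second reply is the omnibus test. It would protect under the global null, but the article does not say that it must be significant before the contrasts are read. Nor would it protect if CSMT truly differed from the control group and not from placebo: the interaction would then be real and could open the gate. The four CSMT-versus-placebo tests at 0.025 would between them carry about 8.3 % error at between-time correlation 0.5, or 6.1 % at 0.8, against the 2.5 % allotted to that comparison.

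Some stronger readings are tempting but not supported:

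- *The error rate is three times 5 %.* That holds only near a correlation of 0.5, with any time point allowed to count and no gate. The article fixes none of these.
- *There are three rival primary analyses.* The trend sentence covers primary and secondary end-points alike and introduces the model from which the contrasts come. It is not a third primary analysis, and Data processing does not itself label follow-up as primary.
- *The follow-up tests at 0.05 raise the primary error further.* If they are secondary, they are outside the primary family.

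**Conclusion.** The point holds as an inconsistency that must be resolved. The abstract defines a primary analysis of eight contrasts, other sections anchor it at the end of intervention, and the threshold pays for two.

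The consequence for error is conditional. It ranges from none (4.7 %), if only the end of intervention is primary, to roughly two to three times the intended 5 % (about 11 to 15 % for correlations of 0.8 to 0.5), if the abstract governs, any time point may count and no gate applies. The figures assume two-sided tests and a global null. The sample size is right for its own inputs and is not in question.

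**What to change.** State one primary contrast per comparison: change in headache days from run-in to the end of intervention, CSMT versus placebo and CSMT versus control, each tested at 0.025. Classify the 3-, 6- and 12-month contrasts as secondary, and claim durability for a comparison only if its end-of-intervention test is significant. Remove follow-up from the abstract's primary-analysis sentence. Say in the Table 2 note that the repeated points 1 and 2 are secondary. In Data processing, say whether the omnibus interaction test is descriptive or a gate, and tie the 0.025 rule to the end of intervention.

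The cost is wording only, and 20 per group is unchanged because it already assumes two tests at 0.025. The real downside is that a benefit appearing only at follow-up could not be claimed as a primary result. If the sponsor wants that claim, adjusting for all eight contrasts is a workable alternative at 28 per group, which the planned 120 covers with up to 30 % drop-out.

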## Background

The prevalence of cervicogenic headache (CEH) is low and varies from 1.0 to 4.6 % in the general population, depending on the applied diagnostic criteria, i.e. 1.0 % if 6 and 4.6 % if 5 diagnostic criteria of the Cervicogenic Headache International Study Group are fulfilled, and 2.5 % if the criteria of the International Headache Society (IHS) are applied (Table 1) (Nilsson 1995a; Pareira Monteriro 1995; Sjaastad et al. 1998; Sjaastad and Bakketeig 2008; Headache Classification Subcommittee of the International Headache Society 2013). Headache disorders have substantial health and socio-economic costs (Vos et al. 2012). However, no studies have exclusively investigated the costs for CEH.

**Table 1 Tab1:** Diagnostic criteria for cervicogenic headache by the Cervicogenic Headache International Study Group

Major criteria^a^
1. Symptoms and signs of neck involvement
a. Precipitation of head pain, similar to the usually occurring one:
i. By neck movement and/or sustained awkward head positioning, and/or:
ii. By external pressure over the upper cervical or occipital region on the symptomatic side
b. Restriction of range of motion (ROM) in the neck
c. Ipsilateral neck, shoulder, or arm pain of a rather vague nonradicular nature or, occasionally, arm pain of a radicular nature.
2. Confirmatory evidence by diagnostic anesthetic blockade
3. Unilaterality of the head pain, without side shift
Head pain characteristics
4. Moderate-severe, non-throbbing, and non-lancinating pain, usually starting in the neck. Episodes of varying duration, or: fluctuating, continuous pain
Other characteristicsof some importance
5. Only marginal effect or lack of effect of indomethacin. Only marginal effect or lack of effect of ergotamine and sumatriptan. Female sex. Not infrequent occurrence of head or indirect neck trauma by history, usually of more than only medium severity.
Other features of lesser importance
6. Nausea. Phonophobia and photophobia. Dizziness. Ipsilateral “blurred vision”. Difficulties swallowing. Ipsilateral oedema, mostly in the periocular area

Diagnostico criteria for cervicogenic headache by the International Classification of Headache Disorders-II
A. Pain, referred from a source in the neck and perceived in one or more regions of the head and/or face, fulfilling criteria C and D
B. Clinical, laboratory and/or imaging evidence of a disorder or lesion within the cervical spine or soft tissues of the neck known to be, or generally accepted as, a valid cause of headache
C. Evidence that the pain can be attributed to the neck disorder or lesion based on at least one of the following:
i Demonstration of clinical signs that implicate a source of pain in the neck
ii Abolition of headache following diagnostic blockade of a cervical structure or its nerve supply using placebo- or other adequate controls
D. Pain resolves within 3 months after successful treatment of the causative disorder or lesion

^a^It is obligatory that one or more of phenomena 1a–c are present

CEH is a symptomatic headache characterized by primarily chronic and usually unilateral headache as well as symptoms and signs of neck involvement (Sjaastad et al. 1998; Sjaastad and Fredriksen 2000; Bogduk and Govind 2009). CEH is often worsened by neck movement, sustained awkward head position, external pressure over the upper cervical or occipital region on the symptomatic side (Pareira Monteriro 1995; Sjaastad and Fredriksen 2000). Abolition of the headache following diagnostic anaesthetic blocks of cervical structures or local factors in the neck gives evidence that the pain is attributed to a neck disorder or lesion (Pareira Monteriro 1995; Sjaastad and Bakketeig 2008; Bogduk and Govind 2009).

Pharmacological management is the first treatment option for CEH despite the limited effect. The risk of medication overuse due to frequent headache attacks represents therefore a major health hazard and both direct and indirect cost concerns. The prevalence of medication overuse headache (MOH) is 1–2 % in the general population (Grande et al. 2008; Aaseth et al. 2008; Jensen and Stovner 2008), i.e. about half the population suffering chronic headache (15 headache days or more per month) have MOH (Lundqvist et al. 2012).

Diversified technique and Gonstead method are the two most commonly used chiropractic manipulative treatment modalities in the profession, used by 91 and 59 % of chiropractors, respectively (Cooperstein 2003; Cooperstein and Gleberson 2004), along with other manual and non-manual interventions, i.e., soft tissue techniques, spinal and peripheral mobilization, rehabilitation, postural corrections and exercises as well as general nutrition and dietetic advises.

A few spinal manipulative therapy (SMT) randomized controlled trials (RCTs) using the Diversified technique have been conducted for CEH, suggesting an effect on headache frequency, headache duration, headache intensity and medicine consumption (Nilsson 1995b; Nilsson et al. 1997; Jull et al. 2002; Haas et al. 2004, 2010; Borusiak et al. 2010). However, common for previous RCTs are the methodological shortcomings, such as; inaccurate headache diagnosis, i.e., questionnaire-based diagnoses used are imprecise (Rasmussen et al. 1991), inadequate or no randomization procedure involved, lack of placebo group, and primary and secondary end-points not pre-specified (Vernon 1995; Chaibi and Russell 2012; Fernandez-de-las-Penas et al. 2006). In addition, previous RCTs mostly included participants with infrequent CEH attacks and did not adhere to the guidelines from the IHS (Tfelt-Hansen et al. 2000; Silberstein et al. 2008). At present, no RCTs have applied the Gonstead method. Thus, considering the methodological shortcomings in previous RCTs, a clinical placebo-controlled RCT with improved methodological quality remains to be conducted for CEH.

Although CEH is the headache we best understand, the SMT mechanism of action is unknown. It is argued that CEH might originate from a complexity of nociceptive afferent responses involving the upper cervical spine (C1, C2 and C3), leading to a hypersensitivity state of the trigeminal pathway conveying sensory information for the face and much of the head (Kerr 1972; Bogduk 2004). Research has thus, suggested that SMT may stimulate neural inhibitory systems at different spinal cord levels and might activate various central descending inhibitory pathways (McLain and Pickar 1998; Vernon 2000; Vicenzino et al. 2001; Boal and Gillette 2004; De Camargo et al. 2011). However, although the proposed physiological mechanisms are not fully understood, there are likely additional unexplored mechanisms which could explain the effect that SMT has on mechanical pain sensitisation.

The objective is to investigate the efficacy of CSMT vs. placebo (sham manipulation) and controls (continue usual pharmacological management without receiving manual intervention) for CEH in a RCT.

## Methods and design

This is a single-blinded placebo-controlled RCT with three parallel groups (CSMT, placebo and control). Our primary hypothesis is that CSMT gives at least 25 % reduction in average number of headache days per month (30 days) as compared to no change in the placebo and the control group from baseline to the end of intervention, and we expect the same reduction to maintain at 3, 6 and 12 months follow-up. If the CSMT treatment is effective, it will be offered to participants whom received placebo or control after study completion, i.e., after 12 months follow-up. The study will adhere to the recommended clinical trial guidelines from the IHS (Tfelt-Hansen et al. 2000; Silberstein et al. 2008), and the methodological CONSORT guidelines (Moher et al. 2010).

### Patient population

Participants will be recruited in the period September to October 2012 through Akershus University Hospital and Innlandet Hospital Trust, Norway. Participants will receive posted information about the project followed by a short telephone interview.

Eligible participants are between 18 and 70 years of age and have at least one headache attack per month. Participants are diagnosed according to at least three major criteria not including occipital nerve blockage from the diagnostic criteria of the Cervicogenic Headache International Study Group (Sjaastad et al. 1998; Knackstedt et al. 2010). All participants are diagnosed by a neurologist.

Exclusion criteria are contraindication to SMT, spinal radiculopathy, pregnancy, depression and CSMT within the previous 12 months. Participants whom during the RCT receive any manual interventions by physiotherapists, chiropractors, osteopaths or other health professionals to treat musculoskeletal pain and disability, including massage therapy, joint mobilization and manipulation (French et al. 2011), changed their prophylactic headache medicine or pregnancy will be withdrawn from the study at that time and be regarded as drop-outs.

In response to initial contact, participants fulfilling the inclusion criteria will be invited to further assessment by the chiropractic investigator. The assessment includes an interview and a physical examination with special emphasis on the whole spinal column. Oral and written information about the project will be provided in advance and written consent will be obtained from all accepted participants during the interview by the clinical investigator. In accordance with good clinical practice, all patients will be informed about the harms and benefits as well as possible adverse reactions of the intervention primarily including local tenderness and tiredness on the treatment day. No serious adverse events have been reported for the chiropractic Gonstead method (Cassidy et al. 2008; Tuchin 2012). Participants randomized into active or placebo interventions, will undergo a full spine radiographic examination and be scheduled for 12 intervention sessions. The control group will not be exposed to this assessment.

